# eRegCom—Quality Improvement Dashboard for healthcare providers and Targeted Client Communication to pregnant women using data from an electronic health registry to improve attendance and quality of antenatal care: study protocol for a multi-arm cluster randomized trial

**DOI:** 10.1186/s13063-020-04980-1

**Published:** 2021-01-11

**Keywords:** Attendance, DHIS2, Quality of care, Antenatal care, Maternal and newborn health, eHealth, Digital health, Electronic registry, eRegistries, Health systems, SMS, Audit and feedback, Effective coverage, Targeted Client Communication, Palestine

## Abstract

**Background:**

This trial evaluates interventions that utilize data entered at point-of-care in the Palestinian maternal and child eRegistry to generate Quality Improvement Dashboards (QID) for healthcare providers and Targeted Client Communication (TCC) via short message service (SMS) to clients. The aim is to assess the effectiveness of the automated communication strategies from the eRegistry on improving attendance and quality of care for pregnant women.

**Methods:**

This four-arm cluster randomized controlled trial will be conducted in the West Bank and the Gaza Strip, Palestine, and includes 138 clusters (primary healthcare clinics) enrolling from 45 to 3000 pregnancies per year. The intervention tools are the QID and the TCC via SMS, automated from the eRegistry built on the District Health Information Software 2 (DHIS2) Tracker. The primary outcomes are appropriate screening and management of anemia, hypertension, and diabetes during pregnancy and timely attendance to antenatal care. Primary analysis, at the individual level taking the design effect of the clustering into account, will be done as intention-to-treat.

**Discussion:**

This trial, embedded in the implementation of the eRegistry in Palestine, will inform the use of digital health interventions as a health systems strengthening approach.

**Trial registration:**

ISRCTN Registry, ISRCTN10520687. Registered on 18 October 2018

## Background

Scale up of effective, high-quality interventions is essential in order to reach the Sustainable Development Goals and achieve Universal Health Coverage in maternal and child healthcare [1, 2]. Antenatal care (ANC), postpartum care (PPC), and newborn care in low- and middle-income countries show low effective coverage [3, 4].

Countries can improve healthcare systems by exploiting the potential of digital technology. Digital health information systems with individual-level data and mobile technologies are expanding globally and provide an opportunity to support, involve, and influence healthcare providers and their clients’ behavior [5–7]. However, effective digital health interventions are complex and require careful design, implementation, and evaluation [8].

Audit and feedback, widely used quality improvement interventions, allow healthcare providers to assess and adjust their performance and, as a result, improve the quality of the care they deliver [9, 10]. Audit and feedback can be defined as any summary of clinical performance of healthcare over a specified period of time and may include recommendations for clinical actions [11]. It is most effective when it is presented more than once, given both verbally and in writing, provided by a supervisor or respected colleague, presented with clear goals and action plans, aimed to decrease targeted behavior, directed towards the recipient with room for improvement, and to health professionals typically working with guideline-bound clinical activities [12]. The model of actionable feedback emphasizes that feedback should be timely, individualized, non-punitive, and meaningful to the recipient to be effective [13]. Explicit use of theory to inform intervention development, and user involvement in all stages of a digital health intervention development, implementation, and evaluation, is recommended, but seldom described [14–17].

Digital Targeted Client Communication (TCC) can utilize data, such as demographic characteristics and health status, to tailor communications to an individual’s specific needs if good-quality individual-level data are available [18, 19]. Short message service (text message (SMS)) is often used as a medium to deliver TCC interventions. Appointment reminders alone, or coupled with generic health promotion messages, can impact people’s knowledge, health literacy, and attitudes and thus improve healthy behavior and utilization of healthcare services [17, 20–23]. However, even though tailored, co-designed, theory-driven TCC interventions tend to be more effective than generic messages, evidence is needed, especially in the field of maternal and child health (MCH) in low- and middle-income countries [15, 19, 21, 22].

### Palestinian context

The total population in Palestine is 4.17 million, 2.58 million (62%) in the West Bank and 1.59 million (38%) in the Gaza Strip [24]. There are approximately 62,000 live births in the West Bank and 56,000 live births in the Gaza Strip annually. Individuals under 18 years of age constitute 48% of the total population, and the fertility rate is 3.8 in the West Bank and 4.9 in the Gaza Strip.

MCH is an important area in the Palestinian healthcare system, and gestational anemia, hypertensive disorders of pregnancy, gestational diabetes mellitus, and fetal growth restriction are identified as priority conditions for prevention [25]. Approximately 43% of pregnant women attend public ANC services, but only 13% according to the recommended national schedule, which results in low effective coverage [26]. Both the utilization and quality of health services have room for improvement. MCH supervisors, each responsible for 16 to 54 public primary healthcare clinics (PHCs), supervise midwives, nurses, and community health workers, mainly by checking registers and clinical equipment [27].

The routine governmental documentation tool for ANC and PPC in Palestine is the eRegistry built on the District Health Information Software 2 (DHIS2) Tracker [28]. The eRegistry is a web-based open-source information system for the longitudinal collection, storage, retrieval, analysis, and dissemination of information on health determinants and outcomes for individual persons [5, 29]. The implementation of the Palestinian eRegistry was carried out by the Ministry of Health (MoH) and the Palestinian National Institute of Public Health (PNIPH), with support from the Norwegian Institute of Public Health and the University of Oslo, as a measure to support healthcare providers in screening and management, and improve monitoring and evaluation [30, 31].

The eRegistry in Palestine provides clinical decision support based on national guidelines, including referral recommendations. It creates longitudinal pregnancy records and removes the need for secondary data reporting or manual aggregation for reporting. The eRegistry’s comprehensive information gathered in a continuous fashion allows TCC via SMS to clients and QID for healthcare providers, but the effectiveness is unknown.

### Objectives

The primary objectives of the eRegCom cluster randomized controlled trial (CRCT) are, compared to the basic eRegistry functionalities in public MCH PHCs in Palestine, to estimate the effectiveness of the eRegistry’s:
Quality Improvement Dashboard (QID) on improving appropriate screening and management for anemia, hypertension, and diabetes during pregnancy by the healthcare providerTargeted Client Communication (TCC) on improving timely attendance to ANC by the womanQiD and TCC interventions combined on the measures described above

We will also estimate the effectiveness across equity measures and, in a sub-sample, assess the effect of the TCC intervention on pregnant women’s worries and perceptions of ANC, including the quality of care and information received from the health system (Fig. 1).

**Fig. 1. Fig1:**
[figure not shown]
The effect of the TCC intervention on pregnant women’s worries in a sub-sample

## Methods

### Trial design

This CRCT is a superiority trial with four parallel arms (TCC, QID, TCC and QID, and control). The unit of randomization is an individual PHC, with the exception of two clusters. These two clusters include two PHCs each, where the pair of PHCs is served by the same healthcare provider.

### Study setting

The most common organizational structure in the public maternal and child healthcare system in Palestine includes two healthcare providers per clinic, mainly midwives, nurses, and/or community health workers, in addition to a doctor serving several clinics. Each user in the governmental eRegistry has a unique username and password, which enable access to records and specific system features according to their assigned role. The woman’s personal ID number is used to create an electronic ANC record for her pregnancy. The sociodemographic, obstetric, and medical information including clinical tests, laboratory, and ultrasound measurement results are entered into the eRegistry at point-of-care. The data trigger different digital health interventions such as the guideline-based clinical decision support and automated public health reports. Women identified with certain risk factors are referred for additional management, and their records are available in the so-called high-risk clinics after referral [31].

### Eligibility criteria

All public PHCs offering ANC and PPC services using the eRegistry were eligible for the study. PHCs that enrolled less than 45 or more than 3000 new pregnancies in 2016 were excluded. No exclusion criteria were made based on individual healthcare provider’s or pregnant women’s characteristics (Fig. 2).

**Fig. 2 Fig2:**
[figure not shown]
Flow diagram showing eligible primary healthcare clinics (PHCs) and allocation

A total of 138 clusters (individual PHC and a combination of two PHCs served by the same healthcare provider for two clusters) were eligible for randomization. They enrolled a mean of 344 and a median of 131 new pregnant women in 2016 (Additional file 1). Data from all ANC visits occurring in the included PHCs during the study period will be used to assess our outcomes.

### Intervention

The interventions are at the cluster-level targeting nurses, midwives, and community health workers, referred to as healthcare providers, and their clients.

#### The Quality Improvement Dashboard intervention

The QID intervention is the provision of access to the QID within their routine eRegistry, as well as training of healthcare providers on how to use it.

As part of the QID intervention development process, public healthcare providers, supervisors, and health system administrators were interviewed to map the existing supervision and feedback system [27]. We found that healthcare providers received irregular supervision visits with limited focus on performance improvement at the clinical level. Findings and recommendations regarding benchmarking [32], the use of SMART (Specific, Measurable, Achievable, Relevant and Timely) criteria, concepts from social nudging and Enhanced active choice [33], and the Model of Actionable Feedback [13] informed the design of the QID. eRegistry users’, nursing and medical directors’, and PNIPH and MoH staff’s reviews informed the revisions. The final version was translated into the local Arabic language.

The training curriculum is founded on quality improvement theories and models such as the Plan, Do, Study, Act (PDSA) cycles [34]. Healthcare providers learn how they can use the QID, which presents indicators of quality gaps in their clinic, as a tool to improve the quality of the care they provide.

The QID includes four tabs for each focus area, namely anemia, hypertension, diabetes, and attendance. Healthcare providers are given a new focus area every week through a message in the eRegistry that congratulates a good performing PHC or presents an evidence-based statement on the week’s focus area. Each tab contains performance indicators calculated from data entered at point-of-care. The indicators are presented as an average over the last 3 months, in both tables and graphs, and benchmarked with clinics within the district. The clinic’s performance level—defined as an index of the absolute and relative values of an overall screening and an overall management indicator—drives the appropriate action items for each focus area. Two screening and two management action items that include recommendations for improvement are presented in colors (green = good performance, yellow = room for improvement, red = large room for improvement) with monthly updates (Fig. 3). The healthcare providers can score the action items via a thumbs up/down icon and add written comments.

**Fig. 3 Fig3:**
[figure not shown]
Quality Improvement Dashboard for anemia to healthcare providers from the eRegistry. Top left: individualized on clinic level; top right: reminders of the week’s focus area, namely anemia, hypertension, diabetes, or attendance; tables: indicators with benchmarks; graphs: percentage average over the last 3 months; right: action items presented in colors (green = good performance, yellow = room for improvement, red = large room for improvement)

#### The Targeted Client Communication intervention

The TCC intervention is automated text messages sent via SMS from the eRegistry to pregnant women, and training of healthcare providers on how to enroll women in the program.

The TCC intervention development process, including the full-text message library, is described in detail elsewhere [35]. In short, pregnant women and healthcare providers were interviewed to identify how pregnant women perceive their risks of getting anemia, hypertension, and diabetes during pregnancy and susceptibility to fetal growth restriction, in addition to benefits and barriers of attending ANC, using the Health Belief Model. The findings, concepts from social nudging and Enhanced active choice [33], and the Model of Actionable Feedback [13] informed the content, medium, timing, and frequency of the TCC intervention.

The training includes how to register and withdraw women, and the timing and the content of the text messages. Healthcare providers register women that agree to receive text messages by ticking a box in the eRegistry. This can be done at any time in gestation, preferably at the first visit.

The tailored text messages include the woman’s name and her clinic’s name and may also include the date of her next appointment (Table 1). Those that include information about one or more of the high priority areas (anemia, hypertension, and diabetes during pregnancy, and fetal growth restriction) will be sent at the time these conditions are screened for, namely at the 16, 18–22, 24–28, 32, or 36 weeks’ gestation routine ANC visit. However, women with documented anemia, hypertension, diabetes, or fetal growth restriction will not receive the information about routine screening for that condition, e.g., women with diabetes will not receive a text message about the routine screening for diabetes at 24–28 weeks’ gestation. The text messages will be sent to the mobile number registered on the woman after working hours during ANC at the following time points:
At registration, a welcome message including information about how to un-enrollOne week prior to a timely scheduled routine visitThree days prior to a timely scheduled routine visit to women with risk factors for anemia, hypertension, diabetes, or fetal growth restrictionTwenty-four hours prior to a visitTwenty-four hours after a missed timely scheduled routine visitRecapture message 24 h prior to the start of the appropriate time window for a routine visit to women without any timely scheduled routine visit in the future

**Table 1 Tab1:** Example text messages send to an overweight pregnant woman without identified anemia, diabetes, or hypertension

Welcome	One week prior to a visit	Three days prior to a visit	Twenty-four hours prior to a visit	Twenty-four hours after a missed visit	Twenty-four hours prior to a missing visit
Dear Abi, Most women attend antenatal care for their own and baby’s health. The healthcare provider will measure your blood pressure, hemoglobin and blood glucose level. You will receive text message appointment reminders. Please let us know if you do not want these messages. Tamoon clinic	Dear Abi, The date of your upcoming appointment is 2020.04.20. One in 20 develop high blood pressure in pregnancy, and this may affect your health and the growth of your baby. The healthcare provider will measure your blood pressure and the amount of protein in urine as they may be a sign of high blood pressure. Tamoon clinic	Dear Abi, 2020.04.20 is your next appointment, as agreed. High body weight before pregnancy, may increase the risk of developing high blood pressure. The healthcare provider will measure your blood pressure and the amount of protein in urine at your next visit. Tamoon clinic	Dear Abi, This is a reminder that you have an appointment tomorrow, 2020.04.20, as agreed. Tamoon clinic	Dear Abi, Sorry to have missed you at yesterday’s appointment. We hope to see you back with us for antenatal care as soon as possible. Tamoon clinic	Dear Abi, You haven’t scheduled your next appointment, which is coming up soon. Timely attendance to every antenatal care visit may ensure you and your baby's safety, through early detection and treatment of complications. Please contact us to schedule your next visit. We are ready to provide you with care, and hope to see you soon. Tamoon clinic

#### Adherence, training, and concomitant care

The TCC and QID interventions in the eRegistry are available to healthcare providers working in PHCs randomized to trial arms receiving one or both of the digital health interventions. The research team trained the trainers, who were eRegistry staff at PNIPH and nursing directors, each representing a governorate. Healthcare providers from TCC and QID intervention PHCs were trained separately, and healthcare providers working in PHCs randomized to both interventions received both trainings. The trainings were conducted in the first quarter of 2019, and each session lasted for half a day. A follow-up training session was conducted in September 2019. Healthcare providers in QID intervention PHCs received a video presenting new functionalities in the QID at the start of the trial. New employees in intervention PHCs will receive on-site training from one of the trainers.

MCH supervisors will carry out similar periodic supervision visits to all PHCs in all arms of this CRCT. Women will not receive any concomitant care across intervention and control PHCs.

### Outcomes

The outcomes represent key areas of quality concerns in Palestine and are in line with our previous eRegQual CRCT, a study assessing the effect of using an eRegistry versus paper-based ANC records [25]. The Palestinian ANC guidelines for the recommended gestational week (Table 2) for screening and management of anemia, hypertension, and diabetes have defined our outcomes. For routine visits recommended for one specific week, we have made the time window for the outcome measures 2 weeks wider than the guideline, to allow some flexibility for maternal choice and time for e.g. laboratory results to be received and documented in the eRegistry.

**Table 2 Tab2:** Time windows for the outcome measures and routine ANC visits including the primary screening test

	First visit	Routine visits				
**Recommended occurrence of ANC visits, GW**	Any week	16	18–22	24–28	32	36
**Included in outcome measures, GW**	Any week ± 7 days	15–17	18–22	24–28	31–33	35–37
**Primary screening tests for priority conditions**^a^	Blood pressure, hemoglobin, urine glucose	Blood pressure, fetal growth	Blood pressure	Blood pressure, hemoglobin, blood glucose	Blood pressure, fetal growth	Blood pressure, hemoglobin, fetal growth

*ANC* antenatal care, *GW* weeks of gestation

^a^Anemia, hypertension, diabetes, and fetal growth restriction according to the Palestinian guidelines

#### Primary outcomes

##### Comparison I: QID arm vs control arm

The primary outcome in comparison 1 is the proportion of women who receive appropriate screening and management of anemia, hypertension, and diabetes (Tables 3, 4, 5, 6, and 7). For example for anemia, the proportion is calculated by identifying the number of ANC visits where anemia should have been screened for and/or managed (denominator), and among them where anemia was appropriately screened for and/or managed (numerator). Only the first step in the management algorithm will be included (Tables 3, 4, 5, 6, and 7). Pregnant women with documented ongoing anemia, hypertension, or diabetes prior to the timely routine visit will not be included in the denominator for appropriate screening and management of anemia, hypertension, and diabetes respectively.

**Table 3 Tab3:** Anemia screening test, result, and appropriate management

Hemoglobin test at first visit, 24–28, and 36 weeks’ gestation		
Hb ≥ 11 g/dL	Hb 10.9–7 g/dL	Hb < 7g/dL
No further action	Hb after 1 month	Refer to hospital

**Table 4 Tab4:** Hypertension screening test, result, and appropriate management prior to 20 weeks’ gestation

Blood pressure prior to 20 weeks’ gestation, test at the first visit and at 16, 18–22 weeks’ gestation	
SBP < 140 mmHg and DBP < 90 mmHg	SBP ≥ 140 mmHg, DBP ≥ 90 mmHg
No further action	Refer to high-risk clinic

*SBP* systolic blood pressure, *DBP* diastolic blood pressure

**Table 5 Tab5:** Hypertension screening test, result, and appropriate management at or after 20 weeks’ gestation

Blood pressure at or after 20 weeks’ gestation, test at 18–22, 24–28, and 36 weeks’ gestation		
SBP < 140 mmHg and DBP < 90 mmHg	DBP 90–99 mmHg, SBP 140–149 mmHg	DBP ≥ 100 mmHg, SBP ≥ 150 mmHg
No further action	New BP within 4 days	Refer to hospital

*SBP* systolic blood pressure, *DBP* diastolic blood pressure

**Table 6 Tab6:** Diabetes screening test, result, and appropriate management prior to 24 weeks’ gestation

Urine glucose test at booking prior to 24 weeks’ gestation	
Negative	Positive
No further action	Blood glucose test

**Table 7 Tab7:** Diabetes screening test, result, and appropriate management at or after 24 weeks’ gestation

Blood glucose test at 24–28 weeks’ gestation		
RBG < 105 mg/dL, FBG < 95 mg/dL	RBG 105–140 mg/dL, FBG 95–126 mg/dL	RBG ≥ 140 mg/dL, FBG ≥ 126 mg/dL
No further action	New blood test within 3 weeks	Refer to a diabetes clinic

*RBG* random blood glucose, *FBG* fasting blood glucose

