##### Comparison III: QID + TCC arm vs control arm

The primary outcome in comparison 3 is the product of the quality of care (comparison 1) and the utilization of care (comparison 2) to assess the effective coverage. For example for anemia, it is the proportion of all timely routine ANC visits where anemia should have been screened for and/or managed, where the woman attended and anemia was appropriately screened for and/or managed.

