### Sample size

Sample size calculations for the primary outcomes were performed in STATA “clustersampsi” (StataCorp. 2015. Stata Statistical Software: Release 14. College Station, TX: StataCorp LP). We estimated the minimum detectable difference for comparison of each intervention arm with the control arm without assuming the effect of multiple comparison (using a single control to each intervention arm). The control prevalence for the primary outcome, using data from the eRegQual CRCT, ranged from 30 to 85% for comparison I (QID vs control) and from 34 to 53% for comparison II (TCC vs control) (unpublished results). The 138 eligible clusters have an average of 172 new pregnancies per 6 months (ranging from 23 to 1500) and a 1.69 coefficient of variation of cluster size (2016 data). We assumed a priori intra-cluster correlation coefficient (ICC) of 0.05 and set the statistical significance level to 5%. We are 80% powered to detect an estimated relative 50% increase for the outcomes with the smallest control prevalence (e.g., improving anemia screening and management at 24–28 weeks’ gestation from 30 to 45%).

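### Table 7 places a random glucose of exactly 140 mg/dL, and a fasting glucose of exactly 126 mg/dL, in two bands that require different actions

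*Protocol article*

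**What the plan says.** The Outcomes section states that the Palestinian antenatal guidelines "for screening and management of anemia, hypertension, and diabetes have defined our outcomes". Tables 3 to 7, under Comparison I, then print the test results and the action that counts as appropriate for each.

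Table 7 covers blood glucose at 24–28 weeks and has three bands:

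| Band | Random glucose (mg/dL) | Fasting glucose (mg/dL) | Scored action |
|---|---|---|---|
| Low | < 105 | < 95 | None |
| Middle | 105–140 | 95–126 | "New blood test within 3 weeks" |
| Top | ≥ 140 | ≥ 126 | "Refer to a diabetes clinic" |

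The middle band is printed as "RBG 105–140 mg/dL, FBG 95–126 mg/dL" and the top band as "RBG ≥ 140 mg/dL, FBG ≥ 126 mg/dL". The Comparison I text adds: "Only the first step in the management algorithm will be included". Comparison III multiplies the Comparison I quality measure by the Comparison II attendance measure, so it inherits the same definition.

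**The concern.** The middle band ends at 140 and 126, and the top band starts at the same two values with equality included. At those values the table requires two different actions. Because only the first management step is scored, no later step settles the matter. A woman at the shared value who was only retested is correctly managed under the middle band and wrongly managed under the top band; a woman who was only referred is the reverse.

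At stake is the scoring of the diabetes component of the Comparison I primary outcome and, through it, Comparison III. The protocol has set these cut points itself and set them inconsistently, so this is not detail left to an analysis plan.

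**Working it through.** **1. Which values are affected.** Each whole-number glucose value from 40 to 399 mg/dL was assigned to the Table 7 bands as printed.

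| Value | Bands met |
|---|---|
| Random 104 | Low |
| Random 105 | Middle |
| Random 139 | Middle |
| **Random 140** | **Middle and top** |
| Random 141 | Top |
| Fasting 94 | Low |
| Fasting 95 | Middle |
| Fasting 125 | Middle |
| **Fasting 126** | **Middle and top** |
| Fasting 127 | Top |

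Random 140 and fasting 126 are the only values in two bands, and no value is without a band.

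**2. Whether the other tables share the problem.** They do not.
- Table 3 (haemoglobin): ≥ 11, then 10.9–7, then < 7. There is no overlap or gap at one decimal.
- Table 4 (blood pressure before 20 weeks): below 140/90, then at or above it. No single measurement lies in two columns.
- Table 5 (blood pressure from 20 weeks): diastolic 90–99 then ≥ 100, systolic 140–149 then ≥ 150. There is no overlap or gap in whole mmHg.
- Table 6 (urine glucose): negative or positive.
- Table 7, lower limit: < 105 then 105, and < 95 then 95. There is no overlap.

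**3. How many tests are affected.** The article gives no glucose distribution, so these inputs are assumptions: random glucose normal with mean 85–105 and SD 15–25 mg/dL (10–51% of tests at or above 105), fasting glucose normal with mean 82–90 and SD 12–15 mg/dL, and results recorded as whole numbers. The share at exactly x is

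P(x) = Φ((x + 0.5 − mean)/SD) − Φ((x − 0.5 − mean)/SD).

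- Random, highest (mean 105, SD 25): Φ(35.5/25) − Φ(34.5/25) = Φ(1.42) − Φ(1.38) = 0.9222 − 0.9162 = 0.0060, or 0.60%.
- Random, lowest (mean 85, SD 15): Φ(55.5/15) − Φ(54.5/15) = 0.999892 − 0.999860 = 0.000032, or 0.003%.
- Fasting, highest (mean 90, SD 15): Φ(36.5/15) − Φ(35.5/15) = 0.99252 − 0.99103 = 0.0015, or 0.15%.
- Fasting, lowest (mean 82, SD 12): 0.004%.

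If results carry one decimal, ±0.5 becomes ±0.05 and the maxima fall to 0.06% (random) and 0.015% (fasting).

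**4. From tests to the outcome.** The denominator counts visits at which screening was due, tested or not. Assuming that 30–100% of due 24–28 week visits have a test, the affected share of due visits runs from 0.003% × 0.3 ≈ 0.001% to 0.60% × 1.0 = 0.60%. If every such woman changed score, the 24–28 week diabetes proportion would move by about 0.6 percentage points. For scale, the Sample size section powers the trial for a change from 30 to 45%, which is 15 points. That example is for anemia at the same visit, so it serves only as a yardstick.

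**The case against.** The strongest case against is that this is loose notation with an obvious reading. The top band carries an explicit ≥ and the middle band is a plain dash range, so a programmer would probably code 140 and 126 as referral. The article also names a governing source, the national guideline, and undertakes under Access to data to publish the syntaxes that recreate the data set. The definition in actual use may therefore be unambiguous.

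Referral is the likelier intent, and nothing here shows that the coded outcome is wrong. The printed table still does not settle it. Elsewhere the document's dash ranges include both ends: in Table 3, 7 must belong to the 10.9–7 band because the next column is < 7, and in Table 5 the 90–99 and 140–149 ranges meet the next column without overlap. By that convention 140 and 126 belong to the middle band, which contradicts the ≥ sign. The guideline is named, but its boundary rule is not given.

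The objection is right about size. Every distributional input is assumed, and the highest figure needs about half of all women at or above 105 mg/dL, every due visit tested, and every affected woman changing score. The normal model also ignores any tendency to record round values such as 140, so 0.6 points is the top of the assumed range and not a strict bound.

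**Conclusion.** The concern holds as a minor error. Table 7 contradicts itself at one random and one fasting glucose value, inside the definition of a primary outcome, and the article supplies no tie-break. Only women at exactly 140 or 126 mg/dL who received exactly one of the two actions are affected. Under the stated assumptions the 24–28 week diabetes proportion would shift by between about 0.001 and 0.6 percentage points.

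Whichever rule is used would apply to all arms, with extraction by blinded analysts, so there is no bias between arms and no change to sample size or power. The existence of the overlap rests on the printed table alone; only its size depends on the assumed distributions, recording precision and tested share.

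**What to change.** Make the shared boundary exclusive in Table 7: middle band random 105 to < 140 and fasting 95 to < 126 mg/dL, with the ≥ sign kept for referral. Check this against the national guideline first. If the guideline refers only above 140 and 126, keep the middle band as printed and change the top band to > 140 and > 126.

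Do not print 139 and 125 as upper limits unless results are known to be whole numbers. If they carry decimals, values between 139 and 140 (up to 0.62% of random tests under the same assumptions) or between 125 and 126 (up to 0.16% of fasting tests) would have no band.

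Fix the same rule in the outcome syntax before allocation codes are released, so that the printed definition and the code agree. The cost is two limits in one table and the matching lines of syntax; data collection, sample size and power do not change.
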